### Sample size

2.4

Sample size estimates are based on the mean and standard deviation of the Pittsburgh sleep quality index^[13]^ scores of patients after 8 weeks of treatment, referencing the pre-test results of 11.24 ± 5.03 for the treatment group and 14.27 ± 5.31 for the control group, set at α = 0.025, one-sided test, β = 0.20. Calculated by PASS 15.0 software to require 47 participants per group. With an estimated drop-out rate of 10%, 53 patients will be included in each group.

### Recruitment strategy and distribution plan

2.5

Participants will be screened among patients attending outpatient clinics and recruitment information will be disseminated through the distribution of brochures and posted on the Internet and WeChat platforms to widen the scope of screening. Participants who meet the inclusion criteria will be fully informed of the purpose and protocol of the study and informed consent signed by the participants will be obtained.

The study will randomly assign patients who meet the criteria for either the treatment group (Baduanjin exercise group) or the control group (Western medicine group) in a 1:1 ratio through a central network-based randomization tool. The random numbers are generated by a statistician using a computer software program and these random numbers are placed in sealed opaque envelopes which are handed to the participants by the study coordinator. Due to the specific nature of the intervention, the patient and the operating physician are knowledgeable about the assigned outcome. However, the assessors of the study results and the statisticians who counted and analyzed the data are unaware of the allocation.

### Interventions

2.6

Patients in both groups will be given health guidance and psychological counseling and maintained their current lifestyle. The treatment group will receive regular Baduanjin exercise. The Baduanjin exercise used in this study is the Baduanjin exercise of Fitness Qigong developed by the General Administration of Sports of China, which consists of 8 main movements. A medical practitioner who has been practicing Baduanjin exercise for 10 years will explain the key points of Baduanjin exercise and give step-by-step instructions to ensure that each patient learns it completely and is issued with a DVD tutorial. Patients will practice at home once a day, 5 times a week, for 30 minutes each time for a total of 8 weeks. The control group will be given oral mirtazapine tablets (N.V. Organon, Netherlands, H20090160) at 15 mg once a day at bedtime, 5 times a week for 8 weeks.

Patients will record in the case report form details of the time taken or practiced, and any discomfort that occurs during the study.

### Outcomes

2.7

(1)Pittsburgh sleep quality index^[13]^: including sleep quality, time to sleep, sleep duration, sleep efficiency, hypnotic medication, sleep disturbance, and daytime functioning. After scoring respectively, the total score is 21. The higher the score, the worse the sleep quality.(2)Hamilton Depression Rating Scale^[14]^: it includes 24 items. The higher the score, the heavier the symptoms.(3)Incidence of adverse reactions: including treatment-related discomfort experienced by patients during the study period.

Two research assistants who are unclear about the outcome of the subgroups will score the 2 groups of patients according to outcome indicators before treatment, at the end of treatment, and at month 1 and month 3 of the end of treatment, through outpatient visits.

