#### Inclusion criteria

2.3.2

(1)Meet the diagnostic criteria for depression and insomnia.(2)Those with a Hamilton Depression Rating Scale score ≥24.(3)Age ≥18 and ≤60 years.(4)Not taking antidepressant or sleep-aid medication (including traditional Chinese medicine and western medicines) within the last 2 weeks.(5)Patient signed an informed consent form.

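### If study mirtazapine is scored under the PSQI hypnotic-medication component, the control arm's week-8 total rises because of its assigned treatment, and the bias favours Baduanjin

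*Protocol article*

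**What the plan says.** All references are to the protocol article.

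- **Outcomes (2.7):** the PSQI covers seven components, "including sleep quality, time to sleep, sleep duration, sleep efficiency, hypnotic medication, sleep disturbance, and daytime functioning". On the scale and its direction: "After scoring respectively, the total score is 21. The higher the score, the worse the sleep quality". It is scored before treatment, at the end of treatment, and 1 and 3 months later.
- **Interventions (2.6):** controls take mirtazapine "at 15 mg once a day at bedtime, 5 times a week for 8 weeks". For the other arm, "The treatment group will receive regular Baduanjin exercise", and no study drug is described.
- **Inclusion criteria (2.3.2):** patients must be "Not taking antidepressant or sleep-aid medication (including traditional Chinese medicine and western medicines) within the last 2 weeks".
- **Sample size (2.4):** the trial is sized on the PSQI after 8 weeks of treatment, with pre-test values of "11.24 ± 5.03 for the treatment group and 14.27 ± 5.31 for the control group", one-sided α = 0.025 and β = 0.20. This gives 47 per group, and 53 with 10% drop-out.
- **Statistical analyses (2.9):** measurement data are compared between groups by t test or Mann–Whitney U test.

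The article does not say that assigned mirtazapine is left out of the medication component, or that a total without that component will be analysed.

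**The concern.** One of the seven components can record the comparator itself. The entry criterion should put the medication component at or near zero in both arms at baseline. From then until the end-of-treatment visit, only one arm is assigned a bedtime drug, given for depression with insomnia. Every control patient or rater who treats that drug as sleep medication adds points to the control total without any change in sleep.

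Higher is worse and the exercise arm has no study drug to count, so this artefact can only favour Baduanjin. It falls on the outcome and time point used for sizing. If the shift is large enough, a significant week-8 difference could partly reflect that controls took their tablets.

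**Working it through.** **Inputs from the article:** means 11.24 and 14.27; SDs 5.03 and 5.31; one-sided α = 0.025; power 0.80; 47 per group; 10% drop-out; seven components; maximum total 21.

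**Assumptions:** the components carry equal weight. The share of controls whose study drug is counted is unknown, and so is the score it would earn. The mean shift is therefore varied over its whole possible range.

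**1. Reproduce the plan's figure.**
- Difference: 14.27 − 11.24 = 3.03.
- Pooled SD: √[(5.03² + 5.31²)/2] = 5.17. Standardized effect: 3.03/5.17 = 0.586.
- Noncentral t, one-sided 0.025: power is 0.794 with 46 per group and 0.802 with 47. So 47 reproduces.
- Drop-out: 47/0.90 = 52.2, rounded up to 53. This reproduces too.

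**2. Bound the artefact.**
- Maximum per component: 21/7 = 3 points.
- Mean shift in controls = share counted × points scored, so between 0 and 3.
- The ceiling is 3/3.03 = 99% of the planned difference.

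**3. Effect on the week-8 test when sleep is the same in both arms.**
- Standard error of the difference: 5.17 × √(2/47) = 1.067.
- Noncentrality = shift/1.067; critical t on 92 degrees of freedom = 1.986.

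| Mean shift (points) | Share of controls if each scores 3 | Noncentrality | Chance of a significant result favouring Baduanjin |
|---|---|---|---|
| 0 | 0% | 0 | 2.5% |
| 0.3 | 10% | 0.28 | 4.6% |
| 0.5 | 17% | 0.47 | 6.7% |
| 0.75 | 25% | 0.70 | 10.3% |
| 1 | 33% | 0.94 | 15.1% |
| 1.5 | 50% | 1.41 | 28.5% |
| 2 | 67% | 1.87 | 45.8% |
| 3 | 100% | 2.81 | 79.5% |

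The table holds the SD at 5.17. If some controls score 3 and the rest 0, the control SD widens, but the results hardly move: 15%, 28% and 45% when one third, one half and two thirds count the drug.

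**4. Planning difference.** The article does not say what the pre-test control group received, so it is unknown whether 3.03 contains any of this artefact. As conditional arithmetic only: if 1 point did, the remaining 2.03 would have 47% power at 47 per group; if 2 points did, the remaining 1.03 would have 16%. No six-component SD is given, so a revised sample size cannot be computed from the article.

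**The case against.** The strongest reply is that the premise is not established. The article never classes mirtazapine as a hypnotic, and its entry criterion names antidepressants and sleep aids separately. Raters may simply not count it, and the shift would then be zero. This stands, and it is why the point is conditional. Bedtime dosing in patients with insomnia, and the Introduction's description of anti-insomnia drugs as common treatment for this condition, make counting plausible but do not prove it.

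A second reply is that scoring rules belong in a rater manual or analysis plan, which is not shown. That would dispose of a complaint about missing detail. It does not dispose of this one, because the composition of the outcome is stated and, with the stated comparator, makes the arms differ by design on one component.

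Third, the damage is limited. By months 1 and 3 the 8-week course has ended, so the PSQI there should be largely spared. The Hamilton score is not affected by this scoring route.

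Three stronger readings are tempting, and the documents do not support them:

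- **That controls will score 3 points higher.** Three is a ceiling that needs every control to receive the maximum. The article does not say that use five times a week earns the top score.
- **That the pre-test difference is already contaminated.** The pre-test control treatment is not described.
- **That the medication question unblinds the assessors.** The article says "Two research assistants who are unclear about the outcome of the subgroups will score the 2 groups". A patient's answer could reveal the arm, but only if the study drug is reported in that item, and nothing in the article shows that it will be.

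**Conclusion.** The concern holds in conditional form. The week-8 PSQI total, as composed, can be raised in the control arm by the assigned treatment, and nothing in the article prevents this. The direction is certain if the drug is counted; the size is not. Under equal weighting the mean shift is anywhere from 0 to 3 points, and the false-positive chance in favour of Baduanjin runs from the nominal 2.5% to 79.5%. It already reaches about 15%, six times nominal, when the mean shift is 1 point. The problem is confined to one outcome at one time point, but that pairing is the one the trial is sized on. It should be fixed before week-8 data are scored. Confidence is moderate, because everything depends on an unstated scoring practice.

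**What to change.** 1. State in advance that assigned study mirtazapine is not scored in the PSQI medication component, and apply the rule in both arms. Sleep medication taken outside the protocol still counts, since it may signal poor sleep in either arm.
2. Pre-specify a week-8 analysis of the sum of the other six components (0 to 18) beside the 21-point total, and show the medication component by arm.
3. Claim a PSQI benefit at week 8 only if the six-component result agrees with the total, with agreement defined beforehand.
4. If component-level pre-test data exist, recompute the planning difference and SD without the medication component and restate the power.

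The cost is small: outcome wording and a re-scoring of items already collected, with no change to treatment or visits. The downsides are that the adjusted score is slightly less comparable with published totals and that the restated power may be lower.

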### Study design

2.1

This is a prospective randomized controlled study to study the efficacy and safety of Baduanjin exercise in the treatment of depression with insomnia. The patients will be randomly divided into a treatment group and control group. The treatment group will take Baduanjin exercise, and the control group will take mirtazapine tablets orally. After 8 weeks of continuous treatment, they will be followed up for 3 months. The flow diagram is shown in Fig. 1. This research scheme follows the latest Consolidated Standards of reporting trials (2017) and standard protocol items: recommendations for interactive trials 2013 statement.

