### Statistical analyses

2.9

Independent statisticians with unclear results for random assignment will be responsible for the statistics and analysis of the data, and the data collected will be statistically analyzed by SPSS 20.0 software. The chi-square test will be used for count data; mean ± standard deviation ($\bar{x}\pm \text{S}$) will be used for measurement data, independent samples *t* test for normal distribution and Mann–Whitney *U*-test for skewed distribution, and differences will be considered statistically significant at *P* < .05.

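### The safety outcome rests on whether discomfort is treatment-related, which cannot be judged between a tablet and an exercise without knowing the arm; the comparison is open to attribution bias

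*Protocol article*

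**What the plan says.** Five statements in the protocol article bear on the point.

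- **Outcome (section 2.7, item 3):** "Incidence of adverse reactions: including treatment-related discomfort experienced by patients during the study period".
- **Raw data (section 2.6):** "Patients will record in the case report form details of the time taken or practiced, and any discomfort that occurs during the study". No relatedness filter applies at this stage.
- **Who knows the arm (section 2.5):** "the patient and the operating physician are knowledgeable about the assigned outcome".
- **Who does not:** section 2.5 says that "the assessors of the study results and the statisticians who counted and analyzed the data are unaware of the allocation", and section 2.7 says that "Two research assistants who are unclear about the outcome of the subgroups will score the 2 groups of patients according to outcome indicators".
- **Test (section 2.9):** "The chi-square test will be used for count data", with P < .05 as the criterion.

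The arms are a home exercise and an oral drug (section 2.1). The article does not say who decides that a discomfort is treatment-related, or how.

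**The concern.** An adverse reaction is an event plus a causal judgement. When the arms are a tablet and an exercise, the same complaint may be attributed to treatment more readily in one arm than in the other. A between-arm difference in reactions can then arise although the events themselves are equally frequent.

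Safety is paired with efficacy in the stated aim (end of the Introduction, section 2.1 and Discussion), so a difference created by classification could be read as one of the trial's findings. The trial also plans to hold a record that avoids the judgement, namely the patients' entries of "any discomfort that occurs during the study". The outcome as worded does not clearly use it.

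**Working it through.** **Step 1: follow an event from patient to outcome.**

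1. The patient, who knows the arm, writes down any discomfort (section 2.6).
2. Someone decides whether it is treatment-related. Neither the person nor the rule is given.
3. Events that pass count towards outcome (3), and the counts are compared by chi-square.

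The article leaves two possibilities for step 2. If the patient or physician decides, the arm is known. If a blinded research assistant decides, that person must either learn whether a tablet or an exercise was given or judge relatedness to an unknown treatment, which has little meaning. The form itself may reveal the arm, because the discomfort is entered alongside the times at which the treatment was taken or practised. Blinding therefore does not remove the attribution step.

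**Step 2: group size.** The article gives no figure for safety. Its group size comes from the Pittsburgh index in section 2.4: difference 14.27 − 11.24 = 3.03; pooled SD √[(5.03² + 5.31²)/2] = 5.172; one-sided α = 0.025; power 0.80. The t-based calculation gives 46.7, so 47 per group, and 47/0.9 = 52.2, so 53. Both stated figures reproduce. I use 47 and 53 below.

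**Step 3: how much difference attribution alone could create.** All event and attribution rates here are assumptions. Let r be the proportion with any event, equal in both arms, and let a_D and a_E be the shares attributed to treatment in the drug and exercise arms. The reported rates are p₁ = r·a_D and p₂ = r·a_E. With mean rate p̄, the approximate chance of two-sided P < .05 is

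Φ{ [ |p₁ − p₂|√n − 1.96√(2p̄(1 − p̄)) ] / √(p₁(1 − p₁) + p₂(1 − p₂)) }.

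Example: r = 20%, shares 80%/40%, n = 53. Then p₁ = 0.16, p₂ = 0.08, p̄ = 0.12, and (0.08 × 7.280 − 1.96 × 0.4596)/0.4561 = −0.70, so Φ = 0.24.

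Reported rates (drug v exercise), then the chance of P < .05 over n = 47 to 53:

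| Any event, both arms | 70%/70% | 70%/50% | 80%/40% | 90%/30% |
|---|---|---|---|---|
| 20% | none induced | 14% v 10%: 9% | 16% v 8%: 22–24% | 18% v 6%: 43–48% |
| 40% | none induced | 28% v 20%: 15–16% | 32% v 16%: 44–49% | 36% v 12%: 79–83% |
| 60% | none induced | 42% v 30%: 23–25% | 48% v 24%: 68–74% | 54% v 18%: 97–98% |

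Swapping the shares between arms gives the same chances with the sign reversed. An all-cause count shows no induced difference in any cell, because r is equal by construction.

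**Step 4: one extreme case.** With r = 20% and shares 80%/20%, the reported rates are 16% and 4%, or 8.5 and 2.1 of 53. For 8 v 2 of 53, Pearson chi-square = 106 × (8 × 51 − 2 × 45)² / (53 × 53 × 10 × 96) = 3.98, P = 0.046. With continuity correction or Fisher's exact test, P is about 0.09 to 0.10. Even here, nominal significance depends on the version of the test.

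**The case against.** The strongest reply is that the article describes blinded outcome assessment and that adverse reactions are one of the listed outcomes. A reader might infer that people who know the arm judge relatedness. The article does not say so: it names no judge, and its text on assessors points the other way. That part of the reply stands. What survives it is that relatedness to a drug or an exercise cannot sensibly be judged without knowing which was given.

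A reader might also infer that the comparison is biased in favour of Baduanjin, since the Introduction warns of drug reactions and describes the exercise as relaxing. That direction is plausible, but without event or attribution rates neither its existence nor its size can be shown.

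A third inference would be that worsening depression in the exercise arm goes unseen. It does not: the Hamilton scale is scored in both arms at four time points, and section 2.3.4 requires the reason for every discontinuation to be recorded.

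Two further replies carry some weight. The word *including* does not strictly confine the outcome to related events, and the any-discomfort record makes an all-event comparison possible. Yet the term adverse reaction implies causation, and the only content given is treatment-related, so the wording at best leaves open what is counted. Second, causality rules and safety tables commonly sit in a full protocol. Their absence is not the complaint here. The outcome definition is stated, and as stated it leans on attribution.

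**Conclusion.** The point holds as a risk, not as a demonstrated bias. The safety outcome is described by treatment-relatedness, neither the person who decides on relatedness nor the rule is stated, patients and physician know the arm, and nominal blinding of assessors cannot make the judgement independent of the arm. The comparison is open to attribution bias of unknown direction and size.

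Under the assumption of equal true event rates, the effect runs from none with equal attribution, through a 9% chance of nominal significance (20% event rate, shares 70%/50%), to 97–98% (60% event rate, shares 90%/30%). These figures show what is possible and do not estimate what will happen in this trial.

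The sample size and the efficacy comparisons are unaffected. The sponsor should change the outcome wording because safety is part of the stated aim and a less exposed outcome is available from planned data.

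**What to change.** In section 2.7, redefine the between-arm safety outcome as the number and percentage of patients with at least one adverse event of any cause, by randomised arm, taken from the any-discomfort record plus the scheduled visits. Report the risk difference with its 95% CI. Show treatment-related events only as a descriptive subset, and state who classifies them and whether that person knows the arm.

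**Cost:** a change of outcome wording and one more table; no new data collection.

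**Downsides:** rates will be higher in both arms and will include complaints unrelated to treatment. The interval will be wide: at an assumed 20% in each arm of 53, its half-width is 1.96 × √(2 × 0.2 × 0.8/53) = 15 percentage points, so a non-significant result would not show equal safety. The change removes the attribution step only. Patients still know their arm when they decide what to write down, so reporting bias remains.

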### Data collection and management

2.8

During the study, personal information about potential and enrolled participants will be collected, shared, and kept in a separate repository to protect confidentiality before, during, and after the trial. Any modifications or changes to the protocol will be reapproved through a formal hospital ethics committee process. An independent clinical research assistant will review the progress of the study on a regular basis. Personnel outside of this research team do not have access to relevant information.

### Statistical analyses

2.9

Independent statisticians with unclear results for random assignment will be responsible for the statistics and analysis of the data, and the data collected will be statistically analyzed by SPSS 20.0 software. The chi-square test will be used for count data; mean ± standard deviation ($\bar{x}\pm \text{S}$) will be used for measurement data, independent samples *t* test for normal distribution and Mann–Whitney *U*-test for skewed distribution, and differences will be considered statistically significant at *P* < .05.

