## Introduction

1

Major depressive disorder is a chronic psychiatric disorder characterized by significant and persistent depression. It is one of the most common mental disorders.^[1]^ Clinical manifestations include persistent depressed mood, slowed thinking, and reduced energy, while some patients may experience loss of appetite, low self-esteem and, in some cases, suicidal tendencies.^[2–4]^ Some studies have shown that the prevalence of major depression in China is 3.02%,^[5]^ while the prevalence of depression in China reaches 7.3% in 2020 as people's life stresses increase with the development of the times,^[6]^ while among adolescents, 24.6% are detected to have depression.^[7]^ Most patients with depression are accompanied by sleep disorders, with 1 survey showing that 90% of patients diagnosed with depression have sleep disorders.^[8]^ On the other hand, insomnia is a potential risk factor for depression, which can aggravate the condition and lead to prolonged depression, thus seriously affecting the patient's life and work, so effective treatment can better alleviate the patient's condition and reduce the huge financial burden on the family and society.

At present, anti-insomnia drugs are often used to treat depression with insomnia, but long-term oral western medicine will produce drug resistance, and the increasing drug dose and adverse reactions of drugs will affect the health of patients. Baduanjin exercise is a traditional Chinese Qigong sport, which emphasizes the integration of body and mind. As a low-energy exercise, Baduanjin exercise can not only enhance the physique, but also regulate people's mood, so that people can reduce pressure and relax in the process of exercising. It has the effect of prevention and adjuvant treatment of physical and mental diseases.^[9,10]^ Although it has been suggested that Baduanjin exercise can improve depression and sleep quality in patients,^[11]^ there are no rigorous randomized controlled studies to evaluate the clinical efficacy of Baduanjin exercise in the treatment of depression combined with insomnia, and there is a lack of long-term follow-up observations. Therefore, this study intends to evaluate the efficacy and safety of Baduanjin exercise in the treatment of depression with insomnia through a prospective randomized controlled trial.

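### Section 2.9 names only two-sample tests for scores taken at four visits, so no named analysis links a patient's visits or estimates whether the week-8 difference lasts to month 3

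*Protocol article*

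**What the plan says.** Section 2.7 (Outcomes) has PSQI and Hamilton scored "before treatment, at the end of treatment, and at month 1 and month 3 of the end of treatment, through outpatient visits". That is four measurements per patient, three of them after treatment.

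Section 2.9 (Statistical analyses) names the methods. For continuous scores, the mean and standard deviation "will be used for measurement data, independent samples" t test applies under normality and the Mann–Whitney test otherwise. Counts go to a chi-square test. Section 2.9 names no repeated-measures method and no arm-by-visit term.

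Section 2.4 (Sample size) rests on PSQI "scores of patients after 8 weeks of treatment", the first post-treatment visit.

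Section 2.3.4 (Discontinuation) asks for a last assessment of discontinued or lost patients, to be used for efficacy and safety. It does not say how that value enters the tests.

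The Introduction gives as part of the rationale that "there is a lack of long-term follow-up observations".

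**The concern.** A two-sample test takes one value per patient. Applied to scores from several visits, it most naturally becomes one test per visit. Two things follow.

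- **Persistence is not estimated.** The trial follows patients for three months partly because long-term observations are lacking, yet no named analysis estimates whether the week-8 difference is kept at month 3. A reader would be left comparing p-values across visits, which is not a test of change.
- **Earlier scores are unused.** A patient with a week-8 score and no month-3 score contributes nothing to a month-3 test unless a value is filled in. If those who stop attending differ between arms in how they were doing at week 8, the month-3 comparison is distorted. Patients know their allocation (section 2.5). Section 2.3.4 also has a discontinuation reason tied to completing the Baduanjin set, which only the exercise arm can meet. Unequal loss is therefore plausible, though not shown.

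**Working it through.** **Inputs from the protocol (section 2.4).** PSQI at week 8 is "11.24 ± 5.03 for the treatment group and 14.27 ± 5.31 for the control group", with the test "set at α = 0.025, one-sided test, β = 0.20". Hence the difference is 14.27 − 11.24 = 3.03, and the SD is √((5.03² + 5.31²)/2) = 5.17. Planned drop-out is 10%.

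**Assumed, because the protocol gives neither.** Between-visit correlation ρ of 0.5 to 0.8, and the loss mechanisms below.

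**1. The plan's own figure.** The protocol states that the calculation came out to "require 47 participants per group". The noncentral t gives power 0.794 at 46 and 0.802 at 47, so 47 reproduces. 47/0.9 = 52.2, rounded up to 53. The sample size is not in question.

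**2. Reading persistence from separate tests (no missing data).** With 47 per arm, SE = 5.17 × √(2/47) = 1.067 and the noncentrality is 3.03/1.067 = 2.84. Suppose the true effect is 3.03 at both visits. Treat the two test statistics as bivariate normal with mean 2.84 each and correlation ρ. The probability that week 8 exceeds 1.96 and month 3 does not is Φ(1.96 − 2.84) − P(both below 1.96):

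| ρ | significant at week 8, not at month 3 |
|---|---|
| 0.5 | 10.9% |
| 0.7 | 8.4% |
| 0.8 | 6.9% |

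In all of these trials the effect has not changed.

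**3. What a direct estimate of the change would give.** SE of the change = 1.067 × √(2(1 − ρ)). At ρ = 0.5 this is 1.07 (95% CI half-width 2.1 points). At ρ = 0.7 it is 0.83 (half-width 1.6). The interval is wide against 3.03, but it shows honestly what the trial can say.

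**4. Bias at month 3.** Simulation with 53 per arm, true effect 3.03, SD 5.17 and 5% random loss before week 8. Later loss in the exercise arm depends on the week-8 score (log-odds 1 per SD, a worse score more likely to leave). Control-arm loss is random at the same overall rate. The table shows the mean overstatement of benefit in points, over 6,000 trials per cell:

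| later loss | two-sample, ρ 0.5 | two-sample, ρ 0.7 |
|---|---|---|
| 5% (about 10% in total, as planned) | 0.12 | 0.16 |
| 10% | 0.26 | 0.31 |
| 20% | 0.44 | 0.61 |

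The likelihood estimate, which uses the week-8 scores, stayed within about 0.03 of the truth in every cell. A separate run of 4,000 trials per scenario gave 0.21 and 0.39 (ρ 0.5) and 0.33 and 0.57 (ρ 0.7) at 10% and 20% later loss. I therefore state that range as 0.2–0.6.

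If control-arm loss also depends on the week-8 score at half the strength, the two-sample bias falls to 0.07–0.09 at 5% later loss and 0.11–0.28 at 10–20%. With equal dependence in both arms it is zero within simulation error.

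**5. Limit of the model.** In a separate simulation, exercise-arm loss depended on the unseen month-3 score, with the loss odds at an average score set to 10% or 20%. The true effect was −3.03. The likelihood estimate averaged −3.34 to −3.87, against −3.64 to −4.12 for the two-sample difference. The bias is smaller but not removed.

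**6. Precision.** Suppose 10% are missing at month 3 for reasons unrelated to outcome, and earlier visits explain 25% to 64% of the month-3 variance. Power then rises from 0.816 to between 0.826 and 0.841. The gain is slight.

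**The case against.** The strongest reply has four parts.

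- **Separate testing is inferred.** Section 2.9 does not say that each visit is tested on its own. A two-sample test could be applied to within-patient change, including change from week 8 to month 3. That is true, but section 2.9 names no such analysis. It does fix the type of test, so a later plan with a mixed model would replace its text rather than fill it in.
- **Discontinued patients may not drop out of the analysis.** A reader might infer that anyone missing a visit is simply excluded. The protocol does not support that, because section 2.3.4 wants a last assessment for the efficacy analysis. Its use is unspecified, and carrying it forward would let an early score stand in for month 3. That point stands, and the fix must deal with it.
- **The planned comparison is hardly touched.** Week 8 is the basis of the sample size and has no earlier post-treatment visit to borrow from. The Discussion also concedes limits on judging long-term effect. Both points stand and limit the weight of the finding.
- **The bias depends on an assumed mechanism in one arm.** This stands too. At planned loss, 0.12–0.16 points is about 0.11–0.15 of the month-3 standard error of 1.06.

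It is also tempting to conclude that the results will favour Baduanjin, or that a mixed model cures the missing-data problem. The protocol gives no loss pattern by arm, so the first is not shown. The second holds only under missing at random.

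**Conclusion.** The point holds in a limited form, as something the sponsor should change rather than a fault that invalidates the trial. The certain part is structural: section 2.9 offers only two-sample tests for scores collected at four visits. No named analysis uses the link between visits or estimates persistence, although long-term observation is part of the rationale.

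The misleading pattern in 7–11% of trials needs no missing data. It rests on the planned effect staying constant and on the assumed correlation. The month-3 bias is conditional: about 0.1–0.2 points at the planned total loss and 0.2–0.6 at heavier later loss, if loss depends on the week-8 score in the exercise arm alone. It is less if the control arm shares that dependence, and zero if the dependence is equal. Sample size and the week-8 comparison are essentially unaffected.

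**What to change.** In section 2.9, analyse PSQI and Hamilton each with one linear mixed model for repeated measures on the three post-treatment visits. Include arm, visit, arm-by-visit and the baseline score as covariate, with an unstructured within-patient covariance and all available scores from every randomised patient. Report the arm difference at week 8, month 1 and month 3, and its change from week 8 to month 3, each with a 95% CI.

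State how the last assessment in section 2.3.4 is used: enter it at the visit nearest to when it was taken, and do not carry it forward.

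Add a sensitivity analysis for data not missing at random, such as a delta adjustment that shifts the missing exercise-arm scores by a range of values. The two-sample test does not serve that purpose, because it needs a stronger assumption than the model does.

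The cost is a paragraph of text and slightly more analysis work on data already being collected, with no change to 47 or 53 per arm. The price is reliance on missing at random, which is weaker than what the two-sample tests assume.
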